### Cost analysis

Unit costing of distinct health care resources will be in accordance with national guidelines (<http://docplayer.nl/6361834-Handleiding-voor-kostenonderzoek-methoden-en-standaard-kostprijzen-voor-economische-evaluaties-in-de-gezondheidszorg.html>). Cost data will be derived as the product sum of health care volume data and their respective unit cost. Observed health utilities based on the EQ-5D health status profiles will be linked to the lengths of the periods in between measurements to derive QALYs. Incremental cost-effectiveness and cost-utility analyses will be performed to calculate the extra cost per additional patient free of local recurrence and the extra costs per additional quality adjusted life year respectively. Differences between groups will be assessed by calculating 95 % confidence intervals for the mean differences after non-parametric bootstrapping, drawing at least 1000 samples of the same size as the original sample separately for each group and with replacement. A cost-effectiveness acceptability curve will be drawn to show the probability of adjuvant chemoradiotherapy being cost- effective at willingness-to-pay values up to €80,000 per QALY. Single and multi-way sensitivity analyses will be performed to study the robustness of these findings to plausible changes in key unit costs and to alternative health utility scoring algorithms [24]. Efficacy and cost data will be discounted to account for time preference.

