Statistical analyses will be performed using SPSS software for Windows version 23 or higher. The one-sided 95 % confidence interval for the between-group difference in locoregional recurrence corresponds to the lower limit of the two-sided 90 % confidence interval for this difference (experimental minus standard). The organ preserving treatment group (intervention) is considered to be non-inferior to the standard treatment group if the one-sided 95 % confidence for the difference in loco-regional recurrence excludes a difference of minus 7 percentage points or farther away from zero in the same direction. For the secondary outcomes as disease free survival and overall survival two-sided 95 % confidence intervals will be calculated. Appropriate summary descriptive statistics will be determined for all secondary endpoints at each visit using raw scores. To assess morbidity the continuous scale of the Comprehensive Complication Index [22] and the categorical Clavien-Dindo classification will be used, for which appropriate statistical tests will be undertaken (the Mann Whitney *U* test, in case of non-normal distribution, and the Chi squared test respectively). For continuous secondary endpoints, either analysis of variance or analysis of covariance models will be used and where necessary, the repeated measures procedure will be implemented. Quality of life data (e.g. EORTC-C30, EORTC-CR29, LARS and EQ-5D) will be graphically represented across all time points and analysed using a repeated measures analysis of variance. All tests based on proportions will be analysed using a logistic regression model with treatment as a factor and, where appropriate, other specified covariates. Time-to-event will be analysed with use of Kaplan-Meier Survival analysis and compared using the log-rank test. The secondary efficacy analysis will be based on the Full Analysis Set (FAS) and the per protocol populations. Significance level is set at an alpha of 0.05 and no adjustment will be made for testing multiple secondary outcomes. Some significant findings are expected to occur by chance so undue consideration will not be given to any particular significant difference. Moreover, interpretation of the results will be based on patterns of differences and in conjunction with the results of the primary analyses.

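### The QALY comparison names no adjustment for starting EQ-5D utility; it is valid on average, but less precise than it could be and off target when starting utility happens to be imbalanced

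*Protocol article*

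**What the plan says.** The Cost analysis section of the protocol article sets out the chain from questionnaire to decision curve.

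- QALYs: "Observed health utilities based on the EQ-5D health status profiles will be linked to the lengths of the periods in between measurements to derive QALYs".
- Comparison of arms: "Differences between groups will be assessed by calculating 95 % confidence intervals for the mean differences after non-parametric bootstrapping". The resampling is done within each arm, with a thousand or more resamples.
- Acceptability curve: the probability that adjuvant chemoradiotherapy is "cost- effective at willingness-to-pay values up to €80,000 per QALY".
- Sensitivity analyses: "robustness of these findings to plausible changes in key unit costs and to alternative health utility scoring algorithms".
- Discounting: "Efficacy and cost data will be discounted to account for time preference", with no rate and no time horizon given.

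No covariate appears anywhere in this section. The Data analysis section does mention covariate adjustment: "For continuous secondary endpoints, either analysis of variance or analysis of covariance models will be used". It does not connect that sentence to QALYs, and it assigns EQ-5D as a quality-of-life measure to repeated-measures analysis of variance. The stratification factors under Methods/Design are age, ASA class, type of initial excision and tumour class; utility is not among them. The article lists clinical follow-up visits from 3 to 60 months but gives no EQ-5D schedule and does not state that a starting measurement is taken.

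**The concern.** A patient's QALY total is utility accumulated over time. The starting utility enters it through the first interval and, more importantly, because patients who start high tend to stay high. If one arm starts higher by chance, part of that gap reappears in the QALY difference, in the cost per QALY and in the acceptability curve. A comparison of arm means cannot separate that part from a treatment effect, and none of the listed sensitivity analyses would reveal it. The repeated-measures analysis of EQ-5D does not help, because it yields a different estimate and does not feed the economic result.

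Cost-effectiveness is a named secondary aim. The trial accepts a slightly higher expected recurrence risk in return for expected gains in morbidity, function and quality of life, and the QALY difference is where that exchange is weighed against cost.

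**Working it through.** **Inputs from the article.** 151 patients per arm (Sample size); acceptability curve up to EUR 80,000 per QALY (Cost analysis). The cost-utility analysis has no precision figure of its own to reproduce. The 151 does reproduce from the article's inputs (98 % and 96 % recurrence-free, margin 7 points, power 80 %) with one-sided alpha 0.05: (1.645 + 0.842)² × (0.98 × 0.02 + 0.96 × 0.04) / (0.07 − 0.02)² = 143.4, and 143.4 / 0.95 = 151.

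**Assumptions, not in the article.** Utility SD 0.20 (range 0.15 to 0.25), the same for starting utility and for average later utility. Correlation ρ between the two 0.5 (range 0.4 to 0.6). Horizon T = 3 years, undiscounted. EQ-5D measured at randomisation.

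**Step 1: size of a chance imbalance.** The SD of the difference in mean starting utility is SD × √(2/n) = 0.20 × √(2/151) = 0.023 (range 0.017 to 0.029).

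**Step 2: what persists into QALYs.** Only the correlated fraction carries forward: shift = ρ × imbalance × T.

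| SD | ρ | Imbalance (one SD) | Shift over 3 years (QALY) | Value at EUR 80,000 per QALY |
|---|---|---|---|---|
| 0.15 | 0.4 | 0.017 | 0.021 | EUR 1,657 |
| 0.20 | 0.5 | 0.023 | 0.035 | EUR 2,762 |
| 0.25 | 0.6 | 0.029 | 0.052 | EUR 4,143 |

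If the horizon were 5 years, the central case would be 0.023 × 0.5 × 5 = 0.058 QALY. The euro figures apply only at the top of the willingness-to-pay range.

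**Step 3: the shift against the reported uncertainty.** The standard error of the unadjusted QALY difference is T × SD × √(2/n) = 3 × 0.20 × 0.115 = 0.069. The central shift is 0.035 / 0.069 = 0.5 standard errors. In general a one-SD imbalance moves the result by ρ standard errors, so by 0.4 to 0.6 here.

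**Step 4: gain from adjustment.** The standard error is multiplied by √(1 − ρ²). At ρ = 0.5 this is 0.866, so the interval is 13 % narrower, which is worth 1 / (1 − 0.25) = 1.33 times the patients for this outcome. At ρ = 0.4 the narrowing is 8 %; at 0.6 it is 20 %.

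**Step 5: bias and coverage.** A simulation of 20,000 trials (143 evaluable per arm, SD 0.20, ρ = 0.5, 3 years, no true difference) gave these results:

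- The mean unadjusted difference was −0.0002 QALY, and coverage of its 95 % interval was 94.9 %.
- The SD of the estimate was 0.071 unadjusted and 0.061 adjusted, a ratio of 0.865, which agrees with step 4.
- Among trials whose starting imbalance exceeded 1.5 SD in either direction (about 13 % of trials), unadjusted coverage fell to about 87 %.

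**The case against.** A reader might infer three stronger things, and the article supports none of them.

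- **That the QALY result is biased.** It is not. Under randomisation the difference in means is unbiased, and its interval already allows for chance differences at the start. A one-SD imbalance of 0.035 QALY lies well inside an interval whose standard error is about 0.07.
- **That a starting imbalance is carried in full through every year.** Only the correlated fraction persists, about half under the central assumption.
- **That the plan excludes adjustment or commits to raw QALYs.** The Cost analysis section is silent on covariates. Resampling within each arm is compatible with a regression inside each resample. This is also a condensed article, and a fuller plan that is not shown may already specify the adjustment.

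The magnitudes can also be questioned. SD, correlation, horizon and questionnaire timing are all assumed. Effects will be discounted, which lowers the 3-year figures. Deaths add variation to QALY totals that starting utility predicts poorly, so the 13 % may be optimistic. Stratifying on age and ASA class may somewhat reduce imbalance in utility.

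These objections limit the point without removing it. The article does more than leave a gap: it names an estimator and a specific list of sensitivity analyses, and neither involves starting utility. Where the article has covariate adjustment in view, in its Data analysis section, it says so. The loss of precision and the lower coverage in imbalanced trials remain.

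**Conclusion.** The point holds as a minor improvement to a secondary economic outcome. As described, the QALY comparison is valid on average with nominal coverage. It is less precise than it could be, and it is conditionally off in a trial where starting utility happens to be imbalanced. With utility SD 0.15 to 0.25, correlation 0.4 to 0.6, 151 per arm and 3 undiscounted years, a one-SD imbalance moves the QALY difference by about 0.02 to 0.05. The exact figures depend on values the article does not give; the direction of the argument does not, as long as starting and later utility are positively correlated. The primary endpoint, the non-inferiority margin and the sample size of 302 are untouched.

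**What to change.** First confirm that EQ-5D is measured at randomisation. The article gives no schedule, but a QALY total counted from randomisation needs that measurement. If a fuller plan already adjusts for it, the article's description only needs to be read alongside that plan.

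Otherwise, add a sentence to the analysis plan along these lines: within each bootstrap sample, drawn by arm as now, the QALY difference is estimated by regression on treatment and starting EQ-5D utility; the adjusted difference is used for the confidence interval, the cost per QALY and the acceptability curve; the unadjusted difference is reported as a sensitivity analysis. Each patient's cost and QALY should stay together in the resampling, which is the ordinary reading of the present text.

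The cost is one sentence and a few lines of code. No patients are added, and no new data are needed if the starting questionnaire is already collected.

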## Discussion

The TESAR-Trial is the first multicentre randomised trial in which patients with a pT1-T2 rectal carcinoma will be randomised after local excision between rectal preserving adjuvant chemoradiotherapy and completion TME. In this non-inferiority trial we hypothesize that rectal preserving therapy for early rectal cancer has similar oncological outcome with significant improved morbidity, function and quality of life compared to conventional radical surgery. The TESAR-Trial is part of a national treatment consortium of multicentre studies founded to create sufficient evidence on the best treatment strategies for early rectal cancer.

The TREC trial from the UK (TEM and Radiotherapy in Early Rectal Cancer) included patients with clinically staged early (cT1-2N0M0) rectal cancer and randomised between radical TME surgery and short course preoperative radiotherapy followed by TEM [REF]. The CARTS phase II Dutch multicentre study prospectively evaluated outcome after chemo-radiotherapy followed by TEM for clinical T1-3N0M0 rectal cancer [25]. Recently it was proposed to combine both initiatives in a new protocol: the STARTREC trial. This study will be conducted parallel to the TESAR trial in the Netherlands. The STARTREC study will be randomizing between intentional organ preserving therapy and radical TME surgery. The STARTREC will include patients based on imaging with the rectal cancer is still in situ. Patients with small tumours staged as T1N0, less then 3 cm can still be treated with initial local excision according to the national guideline. If histopathology shows intermediate risk features, they are eligible for the TESAR trial. Moreover, a large proportion (up to 40 %) of rectal cancer is diagnosed and discussed at the rectal cancer Multi-Disciplinary Team meeting (MDT) after the patient has had an endoluminal local- excision of a lesion that shows infiltrative growth at pathological examination. These excisions might have been polypectomies within the national screening program or an excision of a clinically diagnosed adenoma by for example TEM or EMR [11]. This subgroup of patients can therefore not be included in the STARTREC trial, but will be included in the TESAR. Both TESAR and STARTREC use the same patient reported outcome measurements allowing comparative combined analysis. Together, potentially all patients with early rectal cancer can be included and results from the randomised trials will be powerful to answer which is the best treatment strategy for patients with early rectal cancer.

Current literature on adjuvant chemoradiotherapy after local excision consists of small cohort series which show substantial variability in recurrence rates, ranging between 6 and 43 %, [15–19, 26–34]. Patient selection in these series was often unclear, but often chemoradiotherapy was chosen in patients refusing further surgery or being unfit for completion TME despite they had an incomplete resection or high risk T2 rectal cancer. This explains the relatively high recurrence rates in these series. Furthermore, a variety in adjuvant radiotherapy regimens was used, and none of the studies reported a strict follow-up schedule including digital rectal examination, MRI and endoscopy to allow for early salvage treatment.

Within the TESAR trial, strict pathological selection criteria based on differentiation grade, lymphatic- or vascular invasion and size of the tumour are used in order to include only the intermediate risk group and to exclude patients at high risk of local recurrence. Therefore we expect that the risk of recurrence after adjuvant chemoradiotherapy following local excision will be lower than reported so far. Treatment related morbidity from the chemoradiotherapy is expected to be lower than earlier reported [25]. This is related to the radiation field which is limited to the mesorectum and a lower total dose of 45 Gy than generally applied in more advanced rectal cancer. Additionally, concomitant chemotherapy is only given on weekdays. This less intensive chemoradiotherapy schedule is considered to be oncologically save because only radically removed early rectal carcinomas are included. Nevertheless, patients in the rectal preserving group of the TESAR are expected to have a slightly higher risk of recurrence than the control group. However, this increase is accepted due to the close standardised follow up schedule which allows for early salvage of recurrence. To ensure adequate patient inclusion with the anticipated intermediate risk of recurrence, all specimens of the locally excised tumours are centrally reviewed before a patient can be included in the trial.

In conclusion, due to a shift towards more early staged carcinomas shift and high morbidity of TME surgery, there is an increasing need for less invasive treatment approaches with acceptable oncological outcome. After local excision has revealed a high risk T1 or low risk T2 carcinoma, adjuvant chemoradiotherapy could be an oncological safe alternative for radical surgery, with potential improvements in treatment related morbidity, functional outcome and quality of life. This will prospectively be evaluated in the randomised multicentre TESAR trial.

## Abbreviations

APR, abdominoperineal resection; CCI, comprehensive complication index; DSMB, data safety monitoring board; EMR, endoscopic mucosal resection; ESD, endoscopic submucosal dissection; FAS, full analysis set (FAS); HRQoL, health related quality of life; KWF, Dutch Cancer Society; LAR, low anterior resection; METC, Medical research ethics committee (MREC) (in Dutch, Medisch Ethische ToetsingsCommissie; QALY, quality adjusted life years; TAMIS, transanal minimally invasive surgery; TEM, transanal endoscopic microsugery; TESAR, rectal preserving treatment for early rectal cancer. A multi-centred randomised trial of radical surgery versus adjuvant chemoradiotherapy after local excision for early rectal cancer; TME, total mesorectal excision; TSPM, transanal single-port microsurgery; WMO, WMO: Medical Research Involving Human Subjects Act (in Dutch: Wet Medisch-wetenschappelijk Onderzoek met mensen
